## 3. Groups and Interventions

Participants enrolled in the study will be allocated to one of two groups based on their voluntary acceptance of the telerehabilitation modality:1.TELEREHABILITATION—YES (Remote Group)2.TELEREHABILITATION—NO (In-Person Group)

Both groups will undergo an 8-week individualized CR program based on international guidelines for heart failure rehabilitation [29]. The intervention includes a combined training protocol delivered 5 times per week for the first 4 weeks, and 3 times per week for the subsequent 4 weeks. Each session lasts approximately 60 min and is structured as follows (Table 2):10 min of interval training (warm-up) including flexibility, breathing, and coordination exercises;40 min of endurance training using a stationary bicycle, aiming at 70% of VO_2_ peak (as determined by baseline CPET) or 75–80% of maximum HR if CPET is not available [30,31,32,33,34];10 min of cool-down exercises with stretching and breathing techniques.

## 4. In-Person Group (TELEREHABILITATION—NO)

Sessions are conducted under the direct supervision of a physiotherapist at the cardiac rehabilitation unit of the A.O.U. San Giovanni di Dio e Ruggi d’Aragona. Vital parameters (BP, HR, SpO_2_) are manually recorded; perception of fatigue and dyspnea is assessed using the Borg and Rate of Perceived Exertion (RPE) scales [23,35]. No technological devices are used for remote monitoring.

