## 2. Methods

### Study Design and Population

The TELEREHAB-HF study is a single-center, prospective, observational, non-pharmacological cohort trial designed to evaluate the clinical efficacy of a home-based, supervised cardiac telerehabilitation program in patients with CHF. The trial will be conducted at the tertiary care center Azienda Ospedaliera Universitaria (AOU) “San Giovanni di Dio e Ruggi d’Aragona” in Salerno, Italy, in collaboration with the University of Salerno. The study aims to enroll 220 adult patients (≥18 years) with a confirmed diagnosis of CHF—classified as heart failure with reduced ejection fraction (HFrEF), heart failure with mildly reduced ejection fraction (HFmrEF), or heart failure with preserved ejection fraction (HFpEF)—and functional class I to III according to the New York Heart Association (NYHA) classification. All participants must be clinically stable and on optimized medical therapy for at least one month prior to enrollment (Figure 1).

Participants will be allocated to the telerehabilitation or standard rehabilitation arm based on patient preference and logistical eligibility (e.g., home safety, access to digital devices, internet connectivity). Although this approach does not involve randomization, both groups will be enrolled under identical inclusion and exclusion criteria. To mitigate potential selection bias, comprehensive baseline characterization and statistical adjustment (e.g., propensity score methods) will be applied. Patients in the intervention group (TELEREHABILITATION-YES) will undergo an 8-week individualized cardiac rehabilitation program performed at home, supported by the Khymeia Virtual Reality Rehabilitation System (VRRS). The program includes real-time video-supervised sessions with a physiotherapist, and continuous monitoring through medical-grade wearable sensors that collect electrocardiogram (ECG), heart rate (HR), peripheral oxygen saturation (SpO_2_), and blood pressure (BP) data. The system also records exercise performance using inertial movement sensors, and all data are transmitted securely to a central digital platform for remote clinical oversight and feedback.

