The collected clinical and biometric data will contribute to a translational and “rehabilomics” [17,18] framework, aiming to explore the impact of exercise on the molecular profile of CHF patients. Blood and urine samples will be collected and stored in a biobank for future analysis of biomarkers potentially modifiable by physical activity, thus supporting the identification of individualized rehabilitation strategies.

Patients in the control group (TELEREHABILITATION-NO) will follow a conventional 8-week hospital-based cardiac rehabilitation program under direct supervision. Sessions will be conducted at the outpatient cardiac rehabilitation facility and will include the same structure and intensity of exercise training as the intervention group. Vital signs and effort perception will be assessed and recorded manually using standard clinical tools.

All patients, regardless of group assignment, will undergo standardized evaluations at baseline, and at 4, 8, 16, and 24 weeks.

Prior to the intervention, each participant will undergo a comprehensive clinical evaluation performed by a cardiologist specialized in cardiac rehabilitation—who also serves as the head of the Cardiac Rehabilitation Unit at AOU “San Giovanni di Dio e Ruggi d’Aragona” in Salerno—including clinical examination, ECG, transthoracic echocardiography, and cardiopulmonary exercise testing (CPET) [22,23].

In parallel, physiotherapists will conduct a set of standardized functional assessments, including: 6-Minute Walk Test (6MWT), Short Physical Performance Battery (SPPB), Mini-Mental State Examination (MMSE) for cognitive screening, administration of health-related quality of life (HRQoL) questionnaires, including the Kansas City Cardiomyopathy Questionnaire—12 items (KCCQ-12) and the Short Form Health Survey—36 items (SF-36) [24,25,26,27].

This multidisciplinary assessment ensures that all participants are clinically stable, functionally and cognitively evaluated, and safely eligible to participate in either arm of the rehabilitation program.

Subsequent assessments will include laboratory analyses, including B-type natriuretic peptide (BNP), N-terminal pro B-type natriuretic peptide (NT-proBNP), Serum creatinine, electrolytes (sodium, potassium, chloride), lipid profile, blood glucose.

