## 7. Risk Management and Contingency Planning

To ensure patient safety and address potential risks associated with home-based cardiac telerehabilitation, a structured risk management strategy has been integrated into the TELEREHAB-HF protocol.

Each telerehabilitation session is supervised in real-time by a trained physiotherapist through a digital platform that continuously monitors vital signs using wearable medical-grade sensors. The system tracks SpO_2_, HR, and BP, and provides automatic alerts when pre-defined clinical thresholds are exceeded.

Safety thresholds triggering immediate session interruption and medical evaluation include [1,2,28]:Borg Dyspnea Scale ≥ 8/10Rate of Perceived Exertion ≥ 18/20Resting HR > 120 bpm or <50 bpmSystolic BP > 180 mmHg or <70 mmHgDiastolic BP > 100 mmHg or <50 mmHgSpO_2_ < 88%Sudden fall, acute chest pain, neurological symptoms (e.g., diplopia, motor/sensory deficits, aphasia), altered consciousness

In such events, the physiotherapist halts the session immediately and activates the emergency response protocol, which may include referral to the cardiologist or activation of local emergency medical services (EMS/118).

In case of technical malfunctions or persistent connectivity issues, a fallback mechanism is in place: patients are offered a transition to standard in-person rehabilitation sessions to ensure therapeutic continuity.

All patients receive initial in-person training to become familiar with the devices and the protocol. Those with limited digital literacy are required to have caregiver support as a condition for inclusion. Continuous technical assistance is available throughout the intervention period.

Clinical and biometric data are stored in a secure, encrypted repository, compliant with data protection regulations, ensuring traceability and safety monitoring.

This integrated safety protocol and contingency plan aim to minimize clinical and operational risks, optimize adherence, and ensure high standards of care throughout the rehabilitation pathway (Figure 5).

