## 8. Outcomes

Both groups will undergo standardized assessments at baseline (T0), mid-treatment (4 weeks, T1), post-treatment (8 weeks, T2), and at follow-up timepoints (16 weeks, T3; 24 weeks, T4). Evaluations will include cardiopulmonary functional performance, echocardiographic measurements, biochemical markers, cognitive function, and QoL (Table 3).

The primary outcome of the study is the improvement in functional capacity, assessed as a ≥10% increase in VO_2_max, measured via CPET at 8 weeks (T2).

Secondary outcomes include:QoL: Assessed using the KCCQ-12 and SF-36 at each timepoint.Biochemical parameters: Changes in BNP, NT-proBNP, creatinine, eGFR, serum electrolytes (sodium, potassium, chloride), glucose, and lipid profile.Functional assessments: Performance on the 6MWT and SPPB.Cognitive status: Assessed with the MMSE.Echocardiographic parameters: Left ventricular ejection fraction (LVEF), diastolic function indices (E/A—Ratio of early E to late A ventricular filling velocities; E/e’—Ratio of early transmitral flow velocity to early diastolic mitral annular velocity), and right ventricular function (TAPSE—Tricuspid Annular Plane Systolic Excursion, RVs’—Right Ventricular Systolic Velocity).Adverse events: Monitoring of any complications related to training or telemonitoring (e.g., hypotension, arrhythmias, device issues).

These outcome measures will allow for a comprehensive and longitudinal evaluation of the effects of both in-person and telehealth cardiac rehabilitation on patients with chronic heart failure.

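### The between-arm adverse event test mixes true risk with how events are found, because sessions are monitored differently in the two arms and device issues count as events

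*Protocol article*

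**What the plan says.** **Remote arm.** Study Design and Population describes "continuous monitoring through medical-grade wearable sensors that collect electrocardiogram (ECG), heart rate (HR), peripheral oxygen saturation" and blood pressure. Section 6 lists the K-RING for continuous heart rate and oxygen saturation, and a Health Monitor that provides blood pressure and a single-lead ECG. Section 7 says the system tracks oxygen saturation, heart rate and blood pressure and "provides automatic alerts when pre-defined clinical thresholds are exceeded". Section 7 is framed for the home setting: to "address potential risks associated with home-based cardiac telerehabilitation, a structured risk management strategy has been integrated" into the protocol.

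**In-person arm.** Study Design and Population states: "Vital signs and effort perception will be assessed and recorded manually using standard clinical tools". Section 4 repeats that blood pressure, heart rate and oxygen saturation "are manually recorded; perception of fatigue and dyspnea is assessed using the Borg and Rate of Perceived Exertion (RPE) scales". It also says: "Sessions are conducted under the direct supervision of a physiotherapist at the cardiac rehabilitation unit".

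**Outcome and test.** Section 8 defines the adverse event outcome as "Monitoring of any complications related to training or telemonitoring", with hypotension, arrhythmias and device issues as examples. Table 3 applies it to both interventions and gives events per treatment administered as the unit. Section 9.2 gives the proportion of patients with adverse events as an example of a categorical variable to be compared by Pearson chi-square or Fisher's exact test, at a two-sided 5% level.

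**The concern.** Hypotension, desaturation and many arrhythmias are found by measuring. If one arm is measured more often, or by different means, the same underlying event can be recorded in one arm and missed in the other. The reverse is also possible: a physiotherapist in the room may notice signs that a camera does not show. Device issues add a second asymmetry, because they arise essentially only where the telerehabilitation kit is used.

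Safety is among the aims in the abstract, and Section 10 expects the program to be shown safe. A difference in event proportions could come partly from monitoring, and so could a similarity. The propensity adjustment in Study Design and Population addresses who enters each arm. It cannot correct how events are found once patients are there. Section 12 lists five limitations, and unequal ascertainment is not one of them.

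**Working it through.** **Plan's own figure.** The plan gives no event rate, detection rate or power for the adverse event comparison, so there is nothing to reproduce. The calculation shows only how sensitive the planned test is.

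**Inputs**
- Evaluable patients: 200 (Section 9.3). No allocation ratio is stated; 100 per arm is assumed.
- Test: Pearson chi-square without continuity correction, two-sided 5% (Section 9.2).
- True event risk *r*, equal in both arms: assumed 5%, 15% or 30%. Section 10 says only that a low incidence is expected in the telerehabilitation group.
- Probability that a true event is recorded: assumed 90% remote, and 70% or 50% in person.

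**Formula.** Observed proportion = *r* × detection probability. The rejection rate is the sum, over all pairs of event counts, of the product of the two binomial probabilities wherever the chi-square is significant.

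| True risk, both arms | Detection remote / in person | Observed remote | Observed in person | Rejects |
|---|---|---|---|---|
| 5% | 90/70 | 4.5% | 3.5% | 5.5% |
| 5% | 90/50 | 4.5% | 2.5% | 10.2% |
| 15% | 90/90 | 13.5% | 13.5% | 5.1% |
| 15% | 90/70 | 13.5% | 10.5% | 10.1% |
| 15% | 90/50 | 13.5% | 7.5% | 28.8% |
| 30% | 90/70 | 27% | 21% | 16.7% |
| 30% | 90/50 | 27% | 15% | 55.8% |

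The apparent risk ratio is 0.9/0.7 = 1.29 or 0.9/0.5 = 1.8 at every true risk. Swapping the detection rates between arms gives the same rejection rates with the ratio inverted (0.78 or 0.56).

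**Unequal arm sizes.** At a 20% true risk and 90/60 detection, the test rejects in 22.3% of trials with 100:100 and in 22.2% with 67:133, so the assumed ratio matters little.

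**Masking.** Suppose true risk is 15% remote and 27% in person. With 90/50 detection the observed proportions are 0.15 × 0.9 = 13.5% and 0.27 × 0.5 = 13.5%, and the test rejects in 5.1% of trials. With 90% detection in both arms it rejects in 50.6%.

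**Device issues alone.** Assume 10% of remote patients have one, independently of other events, and that other events are recorded in 20% of both arms. The remote proportion is 1 − 0.80 × 0.90 = 28% against 20%, and the test rejects in 26.2% of trials. This needs no difference in detection, although the 10% is assumed.

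**The case against.** **The monitoring contrast is smaller than it first looks.** Both arms record blood pressure, heart rate, oxygen saturation, Borg and RPE. Section 6 calls only the K-RING continuous, whereas Study Design and Population applies the word to all four signals. A reader might infer automatic arrhythmia detection in the remote arm, but the alert sentence in Section 7 does not name the ECG. This stands, and it narrows the point. The stated difference between sensor and alert monitoring and manual readings remains.

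**Silence in a condensed article.** No session ECG is described for the in-person arm, but none is excluded: Section 4 rules out only devices for remote monitoring. Elicitation and grading of events may be set out in the full protocol. This also stands, so the point rests on what the article does state, namely different monitoring by arm, device issues counted as events, and a test on the proportion with events. Section 9.2 does not say between arms, but these tests for independent groups make that the natural reading.

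**The assumed rates drive the size.** At a 5% risk with 90/70 detection the inflation is negligible. This stands, and it is why a range is given.

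**Monitoring is part of the intervention.** True, and nothing here asks for it to change. The issue is which events the comparative test counts.

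**A stronger reading.** A reader might infer that the test measures only detection intensity, or that nothing can be concluded about safety. The documents do not support that. Symptomatic and serious events are likely to surface in either arm, several Section 7 triggers (falls, chest pain, perceived exertion) need no sensor, and direct supervision may favour detection in person.

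**Conclusion.** The concern holds in a limited form. As written, the adverse event comparison mixes true risk with ascertainment and includes a category that essentially one arm alone can produce. The net direction is uncertain and may differ by event type.

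Under the assumptions shown, false significance ranges from about the nominal 5% (5% risk, 90/70 detection) to 56% (30% risk, 90/50 detection). If adverse events are as infrequent as Section 10 expects, the lower end is the more relevant for the detection problem. All event, detection and device-issue rates are assumptions; the asymmetry itself is in the text. The Table 3 metric, events per treatment administered, would carry the same problem.

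This is a secondary-outcome issue, and the primary endpoint is untouched. It is worth correcting now, because the Data Availability statement says data collection is ongoing and the means of detection may not be recoverable later.

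**What to change.** 1. Add a CRF field for how each adverse event was detected: sensor or alert, manual reading, staff observation, patient report at a session, or questioning at a study visit. Record also whether the session was remote or in person, since Sections 5 and 7 allow remote patients to move to in-person sessions.
2. Limit the between-arm test to events ascertained the same way in both arms: events elicited with the same questions at the common study visits, and unplanned medical contacts or hospitalisations. Some contacts may themselves follow an alert; the detection field identifies them for a sensitivity analysis.
3. Report sensor- or alert-detected events, session interruptions and device issues descriptively by arm, outside the test. Interruptions stay out because an alert can trigger them in the remote arm.
4. State whether the Section 7 thresholds apply to in-person sessions, and reconcile Sections 4 and 7 accordingly. No clinical rule is proposed here.

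The cost is one or two CRF fields, a short set of common questions and some analysis wording. The downside is that fewer events enter the comparative test, so it will be less precise.

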## 5. Remote Group (TELEREHABILITATION—YES)

Sessions are delivered synchronously at the patient’s home via a digital telerehabilitation platform (Khymeia VRRS Home System), enabling real-time audiovisual interaction with the physiotherapist. Patients are equipped with a home-based kit including a tablet, wearable sensors (K-RING, K-SENSOR), a spirometer (K-SPIRO), and a health monitor capable of recording ECG, HR, SpO_2_, and BP. The sensors adopted in the TELEREHAB-HF protocol were selected to ensure clinically relevant, real-time, and multidimensional monitoring of patients during home-based cardiac rehabilitation. These sensors were preferred over alternative solutions (e.g., consumer-grade smartwatches, standalone wearable ECG monitors, or optical motion capture systems) due to their medical-grade certification, full integration with the Khymeia VRRS platform, and ability to support both synchronous feedback and asynchronous data collection. Their interoperability, reliability, and user-friendliness in non-clinical environments make them particularly suitable for patients with chronic cardiovascular conditions undergoing home-based telerehabilitation.

All data are transmitted and stored securely in compliance with data protection regulations. Movement execution is monitored through inertial sensors, and real-time feedback is provided to ensure exercise accuracy. Borg and RPE scales are administered online during sessions.

In both groups, outcome measures (Anthropometric measures, CPET, 6MWT, SPPB, echocardiography, QoL questionnaires, laboratory tests, and MMSE) will be collected at baseline (T = 0), during the intervention (T = 1, at 4 weeks), post-intervention (T = 2, at 8 weeks), and during follow-up at 16 (T = 3) and 24 weeks (T = 4). Patients in the telerehabilitation group experiencing clinical or technical issues may transition to in-person sessions to ensure therapeutic continuity.

## 6. Technological Solution Used for the TELEREHABILITATION—YES Group

The technology used to deliver the telerehabilitation program is the Khymeia System (Virtual Reality Rehabilitation System, VRRS by Khymeia Group, Noventa Padovana, Italy; https://khymeia.com/it/ accessed on 24 February 2025). It is a Class I medical device designed for remote rehabilitation.

During the initial in-person training phase with the VRRS EVO system, the following components and accessories are used.

VRRS EVO system (Figure 2), which includes:A processing unit enclosed in a dedicated cabinet, a capacitive touchscreen LCD monitor, and a low-intensity electromagnetic field generatorWireless 3D passive sensors worn by the patient, detecting position and orientation (6 degrees of freedom) through the electromagnetic fieldThe number of sensors is adapted to specific rehabilitation needs

K-SENSOR: inertial sensors for monitoring movement parametersK-Sensor bands: to support accurate and easy placement of sensors on the limbs during exercisesK-RING: a wearable sensor for continuous monitoring of HR and SpO_2_K-SPIRO: a spirometer for guided respiratory exercises

Health Monitor: for measuring, displaying, and recording body temperature, BP, and single-lead ECG in home or clinical settings.

During the home-based physiotherapy program, following the in-person familiarization with VRRS EVO, the following components are also used:

TeleCockpit System (Figure 3): a high-tech control station for managing all telerehabilitation-related processes, protocols, and sessions. It includes: a height-adjustable, motorized workstation; a control terminal with keyboard and mouse for managing video conferencing and remote control sessions; dual-monitor setup; professional-grade audio-video conferencing system with camera and microphone; professional remote control system.

VRRS Home Kit (Figure 4), enabling home telerehabilitation. This includes:Tablet deviceK-SENSOR inertial sensorsK-Sensor bands for proper placement on limbsK-RING for continuous HR and SpO_2_K-SPIRO spirometer for breathing exercisesHealth Monitor for measuring and storing body temperature, BP, and ECG (single lead)

The Khymeia platform is also equipped with a Kloud service module, enabling full implementation of web-based telerehabilitation services with both synchronous and asynchronous functionality. Key features include:Continuous online updates of connected devices within the hub and spoke networkCentralized sharing of clinical protocols and activities across all devicesReal-time sharing and visualization of patient rehabilitation resultsRemote device allocation and controlAssignment of personalized treatment programs and monitoring of adherence

The telerehabilitation system is modular and supports both clinical and home settings. It has built-in connectivity and enables secure cloud storage of all performed activities. To facilitate ease of use and maximize patient autonomy, all wearable sensors included in the VRRS Home Kit (e.g., K-RING, K-SENSOR) are designed for intuitive application. Each sensor is paired with pre-formed elastic bands or color-coded guides that ensure correct placement on the limbs or chest. During the initial in-person training session, physiotherapists provide step-by-step demonstrations and practical instructions on how to wear and activate the devices. Additionally, the VRRS offers on-screen visual aids and video tutorials accessible at any time during the home-based sessions. For participants with limited digital or motor skills, caregiver support is required, and real-time remote technical assistance is available to troubleshoot any difficulties. These features are intended to reduce the learning curve, improve adherence, and ensure accurate physiological data collection in a non-clinical environment.

